**Methods:**

This is a randomised, double-blind, controlled, multicentre clinical trial designed to evaluate the clinical feasibility of RET for mature permanent teeth with pulp necrosis and to compare the efficacy of i-PRF and blood clots as scaffolds in RET. A total of 346 patients will be recruited from three centres and randomised at an allocation ratio of 1:1 to receive RET with either a blood clot or i-PRF. The changes in subjective symptoms, clinical examinations, and imaging examinations will be tracked longitudinally for a period of 24 months. The primary outcome is the success rate of RET after 24 months. The secondary outcome is the change in pulp vitality measured via thermal and electric pulp tests. In addition, the incidence of adverse events such as discolouration, reinfection, and root resorption will be recorded for a safety evaluation.

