## Methods

### Study design and objectives

This is a randomised, double-blind, parallel positive control, multicentre clinical trial (Fig. 1) that aims to compare the efficacy of i-PRF and blood clots (BCs) as scaffolds in RET for mature permanent teeth with pulp necrosis. The protocol will be reported according to the Standard Protocol Items: Recommendations for Interventional Trials (SPIRIT) statement (Additional file 1). After informed consent acquisition, all eligible patients (*n* = 346) will be randomly divided into two groups at an allocation ratio of 1:1. Patients in the test group will receive RET with i-PRF while those in the control group will receive conventional RET with BC. The follow-up period will be 24 months, and clinical data will be collected at 1, 3, 6, 12, 18, and 24 months after surgery. Figure 2 outlines the schedule of events for patients in the trial.

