#### Dropout criteria

Presence of serious adverse events that doctors believe should lead to termination of trial participation, such as severe internal or external root resorption and tooth fracturePoor clinical complianceWithdrawal of consent for study participation by the patient

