### Outcome measures

Variables will be measured at baseline and at 1, 3, 6, 12, 18, and 24 months after the treatment. At each appointment, a clinical examination, a periapical radiograph, and pulp tests (thermal and electric) will be performed. CBCT images will be obtained at baseline and 24 months after the treatment to evaluate the apical shadow. The primary outcome of this study is the success rate of RET 24 months postoperatively, which will be obtained by evaluating the clinical and radiographic outcomes. The secondary outcomes include the subjective response from the patient to thermal and electric stimuli, which reflects the responsiveness of regenerative pulpal sensory neurons. Safety will be evaluated via the analysis of the presence of adverse events during the study. The evaluators will complete standardised training prior to the study period. Two trained dentists will independently evaluate and disagreements will be resolved through a discussion with a third evaluator.

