#### Safety evaluation

All information regarding adverse events during the study will be recorded in detail, including symptoms, signs, onset time, and severity. Some possible adverse events that may be attributed to RET include reinfection of the root canal, external root resorption, internal root resorption, and discolouration.

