#### Statistical analysis

The data will be analysed by an independent statistician using SPSS 20.0 software (IBM Co., Armonk, NY, USA) at the end of the study to evaluate the evolution. The continuous variables will be described as the mean (standard deviation) or median and analysed using parametric methods. Categorical variables will be described as percentages and analysed using non-parametric methods. The level of significance will be *P* < 0.05, and 95% confidence intervals will be calculated.
*Baseline analysis*

The two groups will be comparable in terms of sex, age, tooth position, disease type, and apical hole size. Quantitative variables will be analysed using a one-way analysis of variance (independent sample t-test) or non-parametric methods if the data do not meet and cannot be transformed to meet parametric assumptions. Qualitative variables will be analysed using the Wilcoxon rank-sum test. A principal component analysis will be performed using multinomial logistic regression to adjust for potential confounders.
(2)*Main outcome analysis*

The inter-group comparison of success rates will be analysed using the chi-square test. If there are baseline variables influencing the comparability of the two groups, a logistic regression model will be used to eliminate the effects of these confounders on the success rate and the odds ratio (OR) will be calculated. For the missing data, the last observation carry forward method will be adopted to fill the validity analysis, that is, the case data that fails to observe the whole treatment process will be transferred to the final result of the test with the last observation data.
(3)*Secondary outcome analysis*

For intra-group comparisons, McNemar’s test will be used to analyse the clinical outcomes of different centres. For inter-group comparisons, the secondary outcome will be analysed using the Chi-square test.
(4)*Safety evaluation analysis*

The adverse events that occur during the study period will be listed for each group and compared using the chi-square test. The security evaluation does not evaluate missing data.

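### Trial participation can be ended for a serious adverse event after treatment is complete, and the safety comparison then treats the shortened follow-up as complete, modestly understating other and later harms

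*Protocol article*

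**What the plan says.** Dropout criteria: the first ground for leaving the trial is "Presence of serious adverse events that doctors believe should lead to termination of trial participation", with severe internal or external root resorption and tooth fracture as examples. What ends is participation in the trial. The trial intervention itself is finished by then, because the scaffold and the final restoration are placed at the second appointment (Interventions, Second Appointment).

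Study design and objectives: "The follow-up period will be 24 months", with visits at 1, 3, 6, 12, 18 and 24 months. Under Outcome measures, each visit has a clinical examination, a periapical radiograph and pulp tests, and a CBCT is taken at 24 months.

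Safety evaluation: "All information regarding adverse events during the study will be recorded in detail", including onset time and severity. Root resorption, reinfection and discolouration are named as possible harms.

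Statistical analysis: for efficacy, "the last observation carry forward method will be adopted to fill the validity analysis". For safety, "The adverse events that occur during the study period will be listed for each group and compared using the chi-square test", followed by "The security evaluation does not evaluate missing data". No allowance for time at risk is mentioned.

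**The concern.** Two of the named harms, external and internal root resorption, are also examples of what can end participation when severe. A safety outcome can therefore stop the observation of safety. Since treatment is already complete, ending participation removes nothing from the patient's trial treatment; it removes only the remaining study visits.

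The chi-square test on events during the study gives a patient last seen at month 3 the same weight as one seen to month 24. For any harm not yet observed, the first patient is scored as event-free for 21 months in which nobody looked. If early exit is more common in one arm, that arm looks slightly safer on the remaining harms. The decision rests on doctors' judgement, and the treating dentists are not blinded (Randomisation, allocation, and blinding). The article does not say which doctors decide, so unequal exit between arms cannot be ruled out.

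At stake are the incidence of individual harms and the later course of the most serious events, in a trial that names safety among its purposes. The scoring of the primary success rate is a separate matter.

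**Working it through.** **No figure to reproduce.** The article states no adverse-event risk, withdrawal rate or safety denominator. From the plan come only the 173 patients per group (Sample size) and the 24 months of follow-up. All rates below are assumptions.

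**Step 1: is the terminating event lost?** Set the passages side by side. Safety evaluation has all adverse events recorded with onset time and severity. Outcome measures says "Safety will be evaluated via the analysis of the presence of adverse events during the study". The analysis compares the events that occur during the study period. The terminating event occurs before the patient leaves and meets all three descriptions, so its loss is zero.

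**Step 2: what is lost through shortened follow-up?** Assume a constant hazard over 24 months, and withdrawal that is independent of the harm and uniformly timed. With true 24-month risk p and withdrawn fraction d:

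- cumulative hazard H = −ln(1 − p)
- chance of seeing the event in a withdrawn patient: q = 1 − p/H
- observed risk = (1 − d)·p + d·q

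Example with p = 10%: H = 0.1054 and q = 1 − 0.10/0.1054 = 0.051. At d = 10%, the observed risk is 0.90 × 0.10 + 0.10 × 0.051 = 9.51%.

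| True risk | 5% withdrawn | 10% withdrawn | 20% withdrawn |
|---|---|---|---|
| 5% | 4.88% | 4.75% | 4.50% |
| 10% | 9.75% | 9.51% | 9.02% |
| 20% | 19.52% | 19.04% | 18.07% |

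The understatement runs from 5 − 4.88 = 0.12 points to 20 − 18.07 = 1.93 points.

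**Step 3: between-arm bias when the true risks are equal.**

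- Withdrawal 5% vs 10%: 4.88 − 4.75 = 0.13 points (true risk 5%) to 19.52 − 19.04 = 0.48 points (true risk 20%).
- Withdrawal 10% vs 20%: 4.75 − 4.50 = 0.25 points to 19.04 − 18.07 = 0.97 points. At a true risk of 10% this is 9.51% vs 9.02%, or 16.5 vs 15.6 events per 173.

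**Step 4: the part due to the adverse-event criterion alone.** Step 2 covers withdrawal for any reason. Suppose 6% of an arm is terminated for an event: 173 × 0.06 = 10.4 patients. If their risk of another given harm is 10%, at most 10.4 × 0.10 = about 1 patient is missed, or 0.6 points, even if all left at time zero. At a 20% risk it is about 2 patients, or 1.2 points. For the count of patients with any adverse event the loss is zero, because each of them already counts.

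**The case against.** The strongest case against is that nothing here is an error. Not imputing adverse events is normal practice, a chi-square test on event proportions is conventional, and the definition of the safety set is usually left to the full protocol or the SAP. Termination depends on medical judgement and is not automatic. The article also does not say in so many words that data collection stops when participation ends, so the full protocol may provide for later safety follow-up. Much of this stands: the missing safety-set definition is no finding, and the numerical effect is small.

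Two things remain. The Dropout criteria state a rule that, in its ordinary meaning, stops observation because of a safety outcome. And no SAP can recover visits that did not take place.

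A reader might go further and infer that patients with missing safety visits are excluded, so that the worst cases vanish. The effect would then be large: 17/173 vs 30/173 (p = 0.041) becomes 15/171 vs 20/163 (p = 0.30) if 2 and 10 serious cases are dropped. The documents do not support this reading. The sentence speaks of missing data and does not mention removing patients. It follows a statement that the events during the study are listed and compared, and it stands in contrast to last observation carried forward for efficacy. Its natural meaning is that safety data are not imputed.

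**Conclusion.** A modest point that holds in limited form. Participation can be ended for a serious adverse event after treatment is complete, and the plain chi-square test then counts the unobserved time as event-free for other harms. The later course of the terminating event is also lost.

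Under assumed 24-month risks and withdrawal rates of 5–20% each, the understatement is about 0.1–1.9 percentage points. Unequal withdrawal (5% vs 10%, or 10% vs 20%) adds about 0.1–1 point of between-arm bias. The part due to the adverse-event criterion alone is probably smaller. These sizes rest on a constant hazard and on withdrawal independent of the harm. The second assumption is doubtful for patients terminated because of an event, so their loss could be larger if they are at higher risk of further harms.

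It would be wrong to conclude that the most severe cases drop out of the comparison, or that every serious adverse event ends participation.

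**What to change.** 1. **Dropout criteria.** Separate the end of participation from the end of data collection: consenting patients who meet the adverse-event criterion keep the study assessments already scheduled to month 24, where the tooth can still be assessed. This is the part that matters most, because censoring in the analysis cannot correct for follow-up that stopped on account of the outcome. It leaves the doctors' decisions about care untouched, and no clinical management rule is proposed.
2. **Statistical analysis, safety evaluation.** Replace the missing-data sentence with wording such as: *Safety data are not imputed. All treated patients, and all events up to last contact including any event that ended participation, are counted.* Add time-to-first-event estimates for each named harm, censored at last contact, as a supplement to the chi-square comparison. This also covers early exit for the other dropout reasons.

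Cost: a few sentences, one more table, and some follow-up effort for the patients concerned. Reported adverse-event rates may come out slightly higher. The Trial status section says recruitment is still in progress, so the change could still preserve data.

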### Ethics and dissemination

The protocol has been approved by the Medical Ethics Committee of NanFang Hospital of Southern Medical University (reference NFEC-2019-233) and registered at ClinicalTrials.gov (reference NCT04313010). Any amendments to the protocol will be reviewed and approved by the ethics committee and funding support departments. Written informed consent will be obtained from all patients. The results will be published in the peer-reviewed journal and presented at conference presentations.

The Data Management Coordinating Centre will oversee the intra-study data sharing process, with the involvement of the Data Management Subcommittee. Only the principal investigator will be given access to all the data with a special password. Other project investigators will have direct access to their own site’s data sets, and other sites’ data by request. To ensure confidentiality, data dispersed to project team members will be blinded to any identifying participant information.

As for ancillary and post-trial care, all the patients who participated in the study could receive compensation from the study unit, including additional medical care, compensation or damages.

## Discussion

As decades of evidence demonstrates the benefits of RET in immature teeth, the technique has recently been extended to mature teeth as an alternative to conventional endodontic treatments [23, 46]. As RET in mature teeth is challenging, there is a lack of long-term clinical trials evaluating the feasibility of RET in mature necrotic teeth. In our study, the feasibility of RET for mature teeth can be tracked longitudinally by comprehensively considering subjective symptoms, clinical examinations, and imaging studies. The feasibility of using i-PRF, a novel and advanced PRF, as a biological scaffold for pulp regeneration will also be investigated. Therefore, this study will explore the feasibility of RET and of RET with i-PRF in mature necrotic teeth and develop a scientific treatment protocol to maximise the potential of i-PRF in RET.

Platelet products have shown great potential in regenerative medicine due to their potency in storing and releasing biologically active substances, regulating the innate immune response, and combatting infection [24–27]. Therefore, several studies regarding the potential of platelet products for pulp regeneration have been conducted. Platelet-rich plasma (PRP), 95% of which is platelets, is the first-generation platelet concentrate [47]. PRP can promote endothelial progenitor cells to form vessel-like structures [48] and the regeneration of pulp-like tissue [48, 49] in immature teeth. However, the protocol for harvesting PRP involves the use of anticoagulants and multiple centrifugation steps with high g-forces [27, 28], and growth factors are released from PRP in a burst-like kinetic manner [50, 51]. As a result, PRF, the second-generation platelet concentrate derived from patient venous blood through single-step centrifugation, has emerged as a purely natural autologous fibrin matrix with trapped platelets and leukocytes, guaranteeing the prolonged release of growth factors and cytokines [19, 28, 29]. Since then, there are increasing researches devoted to optimising the protocol to obtain better platelet concentrates to meet different clinical needs. Leukocyte- and platelet-rich-fibrin (L-PRF), the first blood-derived PRF matrix without anticoagulants, has the potential to improve tissue healing in clinical cases [26, 31, 52–54]. Then, based on lower centrifugation speeds, advanced PRFs (A-PRF and A-PRF+) have been developed with a porous structure and more neutrophilic granulocytes [28, 29, 45]. Thus, the LSCC has been developed [55–57] to obtain PRF with a higher pro-regenerative potency. In 2014, i-PRF was developed. As a flexible matrix, i-PRF overcomes the limitations of the solid PRF matrix [31–33]. Thus, i-PRF has potential as an optimal scaffolding material in RET in mature teeth. Randomised controlled clinical trials are needed to provide high-quality evidence to evaluate the feasibility of RET with i-PRF and, at the same time, explore the standard clinical protocol.

One of the challenges of performing RET in mature permanent teeth is that there is no agreement in the size of the apical foramen for new tissue to grow into the canals. Earlier, it was been found that foramens smaller than 1 mm (measured on radiographs) would prevent the revascularization of the pulp tissue [58]. As a result, many endodontists preferred to mechanically prepare the root canal to a large apical size when performing RET on mature teeth. An animal model study reported that an apical foramen 0.32 mm in diameter did not prevent revascularization and ingrowth of new tissue into canals after transplantation [59]. A range of apical foramen diameters have been attempted in the previous reports of RET on mature teeth, including 1.0 mm [11], 0.6 mm [6], and 0.4 mm [9]. With the deepening of research, it has been revealed that enlargement of the apical foramen to at least 1 mm in diameter is unnecessary for RET [9]. Thus, in this study, we plan to use the conventional canal preparation protocol and avoid excessive preparation, which can increase the risk of root fracture.

The clinical efficacy of RET for mature necrotic teeth depends heavily on disinfection regimens. In this study, 20 mL of 1.0% NaClO will be used for irrigation with a side-vented needle and an ultrasonic irrigation device to minimise the possibility of extrusion of irrigates into the periapical space and to enhance the disinfection efficacy of NaClO. Following the recommendation from the AAE, NaClO should be flushed away from the root canal with saline to reduce any lingering toxicity [4, 60]. EDTA irrigation will also be applied in this study, as EDTA has been demonstrated to promote the survival of stem cells [61], stimulate the release of growth factors embedded in the dentin matrix, and enhance the odontogenic differentiation of migrated cells and angiogenesis [6]. As for the intercanal medication of RET, the AAE and ESE have issued differing recommendations regarding intercanal medication during RET. The AAE recommends triple antibiotic paste (TAP), consisting of metronidazole, ciprofloxacin, and minocycline, while the ESE recommends the use of non-staining calcium hydroxide due to the risk of crown discolouration caused by TAP [45, 62]. TAP cannot be fully removed from root canal systems via current irrigation techniques, potentially due to its penetration and binding to dentin [63]. Thus, to restrict bacterial regrowth and supply continued disinfection, the root canals will be filled homogeneously to the working length with calcium hydroxide in this study. In addition, unlike most existing studies, iRoot BP Plus will be used as the pulp capping material instead of mineral trioxide aggregrate (MTA), due to its satisfactory biocompatibility, sealing ability, antibacterial activity, and ability to upregulate the expression of mineralization-related genes [64].

Finally, to the best of our knowledge, this is the first multicentre clinical trial to evaluate the clinical efficacy of RET in mature necrotic teeth and to evaluate i-PRF as a novel biological scaffold for pulp regeneration. Although there is a concern that this study does not include histological or morphological analyses to determine the nature of the tissues formed in response to the treatment, this study will provide high-quality evidence guiding the future of RET practice on mature permanent teeth via the comprehensive evaluation of symptoms, clinical evaluations, and radiographic assessments. Therefore, our study will contribute to explore the maximum potential of RET and RET with i-PRF in mature necrotic teeth.

## Trial status

This trial is in the process of recruiting participants.

## Data Availability

The datasets analysed during the current study are available from the corresponding author on reasonable request.

## Abbreviations

RET: Regenerative endodontic therapy
i-PRF: Injectable platelet-rich fibrin
RCT: Root canal therapy
BCR: Blood clot revascularization
PRF: Platelet-rich fibrin
PRP: Platelet-rich plasma
LSCC: Low-speed centrifugation concept
BCs: Blood clots
AAE: American Academy of Endodontics
ESE: European Society of Endodontics
CEJ: Cementoenamel junction
CBCT: Cone beam computed tomography
NaClO: Sodium hypochlorite
EDTA: Ethylene diamine tetraacetie acid
CRF: Case report form
DQF: Data query forms
OR: Odds ratio
TAP: Triple antibiotic paste
MTA: Mineral trioxide aggregrate
